# Heart2Heart: a digital peer support programme for people with heart disease: protocol for a community-based, investigator-blinded randomised controlled trial conducted in Australia

**DOI:** 10.1136/bmjopen-2024-088740

**Published:** 2025-02-13

**Keywords:** Cardiovascular Disease, Coronary heart disease, Social Interaction, eHealth, REHABILITATION MEDICINE, Preventive Health Services

## Abstract

**ABSTRACT:**

**Introduction:**

Cardiac rehabilitation is known to reduce morbidity and improve quality of life in people living with heart disease, however, adherence, access and completion of these programmes is suboptimal. Peer support may offer an opportunity to close this service gap. The aim of the study is to determine whether the effectiveness of a digital peer support programme for people living with heart disease is effective in improving social connectedness, clinical and patient-reported outcomes and experience measures.

**Methods and analysis:**

Heart2Heart is a community-based randomised controlled trial with 6 months follow-up for the primary outcome and 6 and 12 months for secondary outcomes. Approximately 752 adults with a diagnosis of heart disease in the past 12 months will be recruited from the general community and Australian cardiac rehabilitation programmes. Control group will participate in usual care, while intervention group will have access to a 6 months intervention that enables peer support via an interactive mobile application, in addition to usual care. The intervention includes online discussion groups, access to resources and facilitated conversations with health professionals. Primary outcome is social connectedness at 6 months follow-up. Secondary outcomes (6 and 12 months) will be all-cause/cardiovascular disease hospital admissions, all-cause mortality, lifestyle (sufficiently physically active, not smoking, sufficient fruit and vegetable consumption), proportion taking prescribed medications and health service utilisation (medical appointments, cardiac rehabilitation, participation in any other in-person peer support activities). Patient-reported outcome and experience measures including self-efficacy, quality of life, satisfaction and programme engagement will be analysed at 6 months. Process measures will include application analytics, barriers and facilitators to engagement with the intervention from participant’s perspective. An intention-to-treat analysis will be used.

**Ethics and dissemination:**

Ethical clearance was obtained from Western Sydney Local Health District Ethics Committee. Heart2Heart has potential to improve social connectedness and provide a valuable addition to traditional cardiac rehabilitation.

**Trial registration number:**

ACTRN12624000386538.

Strengths and limitations of this studyHeart2Heart is a community-based randomised controlled trial with 6 months follow-up for the primary outcome and 6 and 12 months for secondary outcomes.Heart2Heart will determine effectiveness of a digital peer support programme for people with heart disease on social connectedness based on a validated scale.Self-reported physical activity data will be objectively validated (accelerometers) in a 10% subset of participants.Barriers and enablers to delivery of and engagement with the digital peer support programme will be evaluated via a series of process measures.Intention-to-treat analysis will be conducted by a statistician blinded to group allocation.

## Introduction

 Cardiovascular diseases account for approximately one-third of all deaths globally.^1^ Coronary heart disease (CHD) is the leading cause of death attributable to CVD.^2^ Importantly, of the millions of people who experience acute coronary events each year, around a third occur in people who have prior CHD, and are largely preventable.^3^ Recent data from the SNAPSHOT Acute Coronary Syndrome (ACS) follow-up study found that almost 20% of people admitted to hospital with ACS die within 3 years of discharge and 40% experience another cardiovascular disease (CVD) hospitalisation in the same period.^4^ The most common structured preventive programme following an acute coronary event is cardiac rehabilitation; generally a time-limited outpatient group-based programme designed to deliver support, exercise and education sessions, although in recent years, digital modalities have emerged.^5 6^

Cardiac rehabilitation has been found to reduce new clinical events and improve quality of life and prognosis in people diagnosed with CHD.^7^ Participation in a structured cardiac rehabilitation programme is recommended in leading international guidelines.^8^,^10^ However, cardiac rehabilitation, referral, access and completion remain suboptimal.^11^ Reasons are well documented and include transportation impediments, work and/or social commitments and lack of perceived need.^12^ Furthermore, priority populations including those from culturally or linguistically diverse or low socioeconomic backgrounds are less likely to attend.^12^ Literature also suggests that women are less likely to be referred, to participate and complete cardiac rehabilitation programmes.^13^ At the same time, there are increasing numbers of people surviving initial acute coronary events meaning capacity for efficient and evidence-based support is increasing.^6^ Therefore, improving preventive care options and providing better support to people who both do, and do not, access or complete cardiac rehabilitation is a worldwide priority.^14^

Consumer-driven social networks and peer support programmes have great potential and value in healthcare due to their ability to promote ideas and information sharing between people and provide support in an economically viable manner. The concept of social connectedness has been defined as the ‘degree to which people have and perceive a desired number, quality, and diversity of relationships that create a sense of belonging, and being cared for, valued, and supported’.^15^ Consumer social networks are likely effective because they provide emotional support for behaviour change via social connectedness among members who possess experiential knowledge of similar situations and experiences.^15 16^ Meta-analyses have reported 50% increased likelihood of survival by people with stronger social connections^17^ and cohort studies have found that social isolation is associated with lower CVD screening^18^ and increased fatal first CVD events.^19^ Furthermore, randomised control trials and qualitative research among people postcardiac surgery^20^ and with diabetes have demonstrated the potential value of in-person social support networks in terms of reduced anxiety, better knowledge and improved self-efficacy for adopting healthier choices.^21 22^ However, previous research relating to peer support interventions has largely focused on in-person delivery.^23^ Furthermore, a study among people with diabetes found that a peer support was cost-saving,^24^ and a randomised trial involving men recovering from coronary artery bypass surgery found that the peer support intervention was associated with less health service utilisation; however, the authors highlight that further research in this area is needed.^25^

Advances in technology and affordable mobile phone technology offer an opportunity to maximise effectiveness and reach of preventive healthcare, both primary and secondary. Importantly, evidence suggests that digital health interventions should be consumer-focussed, meaningful and supportive for people who use them.^26^,^28^ A variety of studies have provided evidence that digital strategies have potential to improve access and outcomes while also being cost-effective^29^ and engaging for people with heart disease.^26^ Combining digital advancement and social connection via peer support offers a potentially innovative and scalable approach, but robust research with heart disease survivors is needed. Therefore, the aim of this study is to determine whether a community-based peer support mobile application for people living with heart disease improves social connectedness, hospitalisation, mortality, cardiovascular risk profile (including behavioural, biomarkers and medication persistence) and patient-reported measures. Also, the study aims to understand the perspectives of people with heart disease, clinicians and other stakeholder organisations in terms of barriers and enablers to engagement with peer support. We hypothesise that among people with heart disease, those randomised to a digital peer support programme will experience better social connectedness, health and patient-reported measures at 6 months follow-up than those randomised to usual care.

## Methods and analysis

### Study design

Heart2Heart is a community-based, single-blind, randomised controlled trial (figure 1) with 6 and 12 month follow-up. The study will take place in three Australian states; New South Wales, Victoria and Western Australia from June 2024 to December 2025 (sponsor is University of Sydney). The protocol is reported according to the Standard Protocol Items: Recommendations for Interventional Trials (SPIRIT) Statement^30^ and intervention using the Template for Intervention Description and Replication (TIDieR).^31^

**Figure 1 F1:**
[figure not shown]
Study flow diagram. CONSORT, Consolidated Standards of Reporting Trials; PREMs, patient-reported experience measures; PROMs, patient-reported outcome measures.

### Participants and recruitment

Inclusion criteria are people (1) aged at least 18 years; (2) with a confirmed diagnosis of heart disease, coronary revascularisation procedure or greater than 50% stenosis on coronary angiogram within the prior 12 months and (3) own a mobile device. Exclusion criteria are people (1) with major neurocognitive diagnoses; (2) who are not willing/able to give informed consent and (3) are unable to read or speak English.

Three recruitment strategies will be used to allow varied identification of potential participants via peer support associations, cardiac rehabilitation programmes and direct to consumers. The strategies are as follows: (1) consumer-focussed stakeholder organisations will email members with information about the study and if interested, potential participants can contact the research team for screening and to explore interest in participation; (2) the research team will contact community peer support programmes and promote the study via social media to introduce the trial to explore potential eligibility and interest of eligible people in participating and (3) cardiac rehabilitation coordinators in participating states will identify potential participants from their programmes over the previous 6 months. Research staff will then contact them in-person, via telephone or email to screen for eligibility and explore potential willingness to participate in the study. For all prospective participants, a research staff member will seek consent (online supplemental file 2) (either on paper or e-consent or directly via the mobile application) prior to baseline data collection and randomisation. Taken together, the collective cardiac rehabilitation programmes have approximately 1000 eligible people, the Australian stakeholder organisations have a membership base of over 1000 and the community peer support programmes include an online group (MyHeartMyLife) with approximately 3800 members.

### Randomisation and blinding

After informed consent, participants will be randomised and directed electronically to the online data collection survey. Randomisation will be stratified by regional/rural and urban areas and by those recruited from in-person peer support networks versus not (50:50). An independent statistician will generate the randomisation schedule (then upload into the study Research Electronic Data Capture, REDCap) with allocation sequence concealment strategies implemented. This is single-blind study where investigators, statisticians and research assistants collecting data will be blinded to group allocation; however, participants will know if they are allocated to the digital peer support intervention.

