What	Access to a digital peer support app with four components; Discussion Groups with other people with lived experience of heart disease. The app has three primary discussion groups where participants can go online and introduce themselves and share their (1) general experiences relating to their heart disease journey and care, (2) exercise and diet and (3) memory and thinking. Participants will be able to freely move in and out of these discussion groups depending on their own preference. Ask an expert’ sessions that mimic those commonly available at the in-person peer support group. These sessions will be scheduled monthly for 30 min and include sharing of advice by multidisciplinary clinicians (registered with national relevant national authorities) such as nurses, allied health providers, dietitians and pharmacists. Participants will also be able to ask questions about topics such as exercise and diet, medicine and cognition. Resources are available via virtual folders in the app. Resources include videos and ‘fact sheets’ developed by the National Heart Foundation of Australia, peer support guidelines, the privacy policy and study documents. Fact sheets include resources relating to heart disease risk factors, medications and cardiac rehabilitation. The peer support guidelines cover aspects related to being respectful, inclusive and using appropriate language, promoting a supportive and welcoming community, encouraging a safe space, showing respect and empathy, using language carefully, listening to others a safe space where individuals feel comfortable sharing their stories and challenges.
Who	As a peer support intervention, the intervention is largely driven by conversations and input of other participants who also have lived experience of heart disease. However, the research team will monitor daily for inappropriate content (such as aggressive or inappropriate language or behaviour) and to help facilitate positive and supportive online conversation although content will be driven by the participants themselves.
How	The intervention is delivered online via a stand-along app that is only available to people allocated to the intervention group of this study. It is freely available and has a password-protected login. There is no face-to-face component.

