### Data collection and study outcomes

The data collection schedule and time points for each outcome are summarised in table 2. Data will be collected remotely and entered into a purpose-built online questionnaire using the REDCap software.

**Table 2 T2:** Schedule of Heart2Heart study procedures

	Time point (months)		
Schedule of assessments	0	6	12
Eligibility screen	✓		
Informed consent	✓		
Randomisation/allocation	✓		
Primary outcome			
Social connection in the context of cardiovascular health	✓	✓	✓
Secondary outcomes			
Social connectedness—8-item Social Connectedness Scale^33^	✓	✓	✓
Proportion physically inactive—GPAQ score^34^	✓	✓	✓
Proportion physically inactive—METs accelerometer (10% of participants)	✓	✓	
Point abstinence from smoking—self-report	✓	✓	✓
Proportion of participants consuming alcohol one or more standard drinks per week—self report	✓	✓	✓
Proportion of participants meeting fruits and vegetable guidelines—self-report	✓	✓	✓
Proportion of days covered with guideline-recommended medications—Pharmaceutical Benefits Scheme administrative data	✓	✓	✓
All-cause and CVD hospitalisations—self-report		✓	✓
All-cause and CVD mortality—National Death Index		✓	✓
Health Service Utilisation (medical appointments, cardiac rehabilitation, peer support programmes)—Medicare Benefits Scheme administrative data and self-report	✓	✓	✓
PROMs and PREMs			
Self-efficacy—Self-Efficacy to Manage Chronic Disease Scale—six item^35^	✓	✓	✓
Quality of life—EQ5D-5L^36^	✓	✓	✓
Participant satisfaction/acceptability with peer support programme—purpose built survey	✓	✓	
Digital peer support usage and engagement—analytical app data (page visit, frequency of login, participation in discussion groups, etc) for intervention participants only		✓	

CVDcardiovascular diseaseEQ5D-5LEuroQol 5 dimensionGPAQ, Global Physical Activity QuestionnaireMETsmetabolic equivalentsPREMspatient-reported experience measuresPROMspatient-reported outcome measures

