To verify self-reported physical activity data, a random subset (minimum 10%) of participants (control and intervention), physical activity will be assessed over 24 hours per day for 7 days (prior to baseline randomisation for baseline data), using a GENEActiv V.1.2 wrist-worn sensor which collects continuous accelerometry data via bluetooth. The sensor does not provide feedback to the wearer (no screen), minimising the likelihood of participants’ physical activity being influenced by sensor information. Sensors will be sent to and from participants via mail in a reply-paid envelope, along with instructions on how and when to wear the activity sensor and a logbook to record date and times worn or removed. Once the sensor and logbook are returned, the research team will download data from the tracker in real-time for storage in the study database. These data will be analysed by comparing average minutes per day participant were at least moderately physically active and be the subject of a sensitivity analysis to provide verification of the self-reported physical activity data.

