### Sample size and statistical analyses

A sample size of 752 (376 per group) will achieve over 80% power, allowing for 10% drop-out, to detect a difference in the proportion of participants that feel socially connected between control and intervention groups by 10% at 6 months follow-up where the baseline estimate is based on the British Regional Heart Study, where 27% of participants with pre-existing CVD were classified as having low social engagement.^38^ As reported in a recent scientific state from the American Heart Association, there is consistent evidence for a direct association between social isolation, loneliness and CHD and stroke mortality, but the relationship is complex with unmeasured confounders.^39^ Based on advice from expert clinicians in the area, it was determined that an effect of reduced social isolation for one in 10 people would be clinically meaningful and hence an effect size of 10%.

Analyses will be performed according to the intention-to-treat principle by a statistician blinded to group allocation. Baseline and outcome data will be presented as frequencies and proportions for categorical data and means and SD for normally distributed continuous outcomes or median and IQR intervals for skewed continuous outcomes. Outcomes will be compared between control and intervention groups using all available data with intervention and control groups compared at 6 and 12 months. Normally distributed continuous outcomes will be analysed using the analysis of covariance and categorical outcomes will be compared using a log-binomial regression model, adjusting for baseline value of the outcome variable. Prespecified subgroup analyses will be performed for (1) self-reported gender, (2) regional areas, (3) cardiac rehabilitation completion (at least 50% of sessions offered) versus not and (4) previous or current peer support attendance (has participated in an in-person or other digital peer support programme since January 2024) versus not. The subgroups will be compared by including an interaction term between the subgroups and the randomisation status to the main models as described above.

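### As worded, participants are randomised before the month-0 survey and nothing withholds allocation until it is done, so the self-reported baseline used as covariate can be affected by known allocation

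*Protocol article*

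**What the plan says.** Randomisation and blinding gives the only explicit sequence for the main survey: "After informed consent, participants will be randomised and directed electronically to the online data collection survey". The same section says that "participants will know if they are allocated to the digital peer support intervention".

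Data collection and study outcomes describes how the survey is done: "Data will be collected remotely and entered into a purpose-built online questionnaire using the REDCap software". Table 2 there lists both randomisation and the primary outcome at month 0, with no order within month 0. The primary outcome is built from two self-reported items on connecting with others and feeling togetherness with peers about one's heart health.

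Two other places bear on the order. For a random subset of at least 10%, the 7-day sensor wear is to take place "prior to baseline randomisation for baseline data". Participants and recruitment says that consent is sought "prior to baseline data collection and randomisation".

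Sample size and statistical analyses specifies log-binomial regression for categorical outcomes, "adjusting for baseline value of the outcome variable".

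On the app, the recruitment section allows consent to be given "either on paper or e-consent or directly via the mobile application) prior to baseline data collection and randomisation". Table 1, under How, says the app is "only available to people allocated to the intervention group of this study", and the Control group section says controls have no access to it.

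**The concern.** A baseline covariate is safe to adjust for because treatment cannot have influenced it. That protection is lost if participants answer after learning their group.

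The risk is sharper here than in most trials. The items ask whether the person can connect with others about heart health, and the allocation just disclosed is whether they will receive an app for that purpose. An intervention participant might answer more positively in anticipation. They might also answer more negatively, having been prompted to notice what they lack. Controls may react too. Adjusting for such a value carries the reaction into the treatment estimate.

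Secondly, someone who learns their arm and then does not complete the survey has no baseline value. If this happens more in one arm, baseline non-response is differential.

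Neither problem can be removed afterwards by an analysis plan, because an uncontaminated baseline would never have been recorded.

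**Working it through.** **Order of events, section by section**

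| Place | What it fixes |
|---|---|
| Randomisation and blinding | Consent, then randomisation, then online survey. Time of disclosure not stated. |
| Data collection and study outcomes, accelerometer text | Baseline sensor wear before randomisation, for the subset only. |
| Participants and recruitment | Consent before both baseline and randomisation. Baseline is named first, but the order of the two is not fixed. |
| Table 2 | Both at month 0, no order. |

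So month-0 data fall on opposite sides of randomisation in two sections. For the survey, which carries the primary outcome, the only explicit order is randomisation first.

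**The plan's own figure**

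The article states 752 (376 per group), over 80% power, 10% drop-out, a 10-point difference and a 27% reference rate. Comparing 27% with 37% (pooled variance, 80% power, two-sided 5% assumed) needs 341 per arm. Then 341 × 1.10 = 375.1, rounded up to 376, and 2 × 376 = 752. The figure reproduces and does not depend on the order of procedures. After 10% drop-out, 376 × 0.90 ≈ 338 per arm remain, with 79.7% power for this difference.

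**Size of the possible bias**

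On the risk-difference scale, a baseline-adjusted comparison is approximately:

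adjusted difference = (difference in outcome) − b × (difference in baseline)

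Here b is the slope of outcome on baseline. If disclosure raises the intervention arm's baseline proportion by s, the bias is −b × s. The documents give neither b nor s, so both are assumed: b from 0.2 to 0.5, s from 0.02 to 0.10. Each cell shows the bias in points on a true 10-point effect, then the power at 338 per arm if the remaining difference from 27% is all that is seen.

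| b | s = 0.02 | s = 0.05 | s = 0.10 |
|---|---|---|---|
| 0.2 | −0.4; 76.5% | −1.0; 71.3% | −2.0; 61.4% |
| 0.3 | −0.6; 74.8% | −1.5; 66.5% | −3.0; 50.7% |
| 0.4 | −0.8; 73.1% | −2.0; 61.4% | −4.0; 39.8% |
| 0.5 | −1.0; 71.3% | −2.5; 56.1% | −5.0; 29.6% |

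A true 0.10 is therefore estimated as 0.10 − 0.004 = 0.096 at one end and 0.10 − 0.050 = 0.050 at the other. If the intervention baseline shifts down instead, the sign reverses and the estimate runs from 0.104 to 0.150. With no true effect, the same shifts produce a spurious difference of 0.4 to 5 points in either direction.

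**Cross-check by simulation**

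Repeated simulations used a true 73% versus 83%, correlated normal latent baseline and outcome, and a logistic model standardised to a risk difference. An upward shift of 5 points in the intervention baseline gave adjusted differences of 8.4 to 8.7 points at latent correlation 0.5, and 7.6 to 7.9 at 0.7. These lie within the linear range for s = 0.05, which is 7.5 to 9.0.

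**The case against.** The strongest reply is that a condensed sentence is being read as settled design. It says data collection survey, not baseline survey, and is silent on when allocation is shown. REDCap could assign the arm and reveal it only after the survey. The flow diagram is not available here and might show a different order. This stands as a limit: a reader might infer that allocation-aware baseline reporting is the plan, and the article does not establish that. It does not remove the point, because the first survey after consent can only be month 0 and no section says that disclosure waits.

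Several stronger readings are tempting and not supported:

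- That other sections state the opposite order outright. Only the accelerometer text does, for the subset. The recruitment section merely suggests it by word order.
- That the sensor week is impossible under the stated sequence. Randomisation comes after consent with no immediacy given, so a sensor week could fit between them. The subset's month-0 data would then be split around randomisation.
- That people without a baseline value are dropped from the adjusted analysis. The article says all available data are used and does not say how a missing baseline is handled, which is commonly left to the analysis plan.
- That consent through the app exposes future controls. A consent screen is not forum access, the login is password-protected, and the article places download at the start of the intervention period. Exposure is a possibility, not shown.

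The magnitudes are illustrative. The shifts, slopes and correlations are all assumed, the planned model is log-binomial rather than linear or logistic, and a small shift gives a small bias.

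**Conclusion.** The point holds as a conflict in the stated sequence that, followed literally, leaves the primary analysis open to bias. The article randomises unblinded participants before the survey that supplies the model's baseline covariate, does not withhold allocation, and gives the reverse order for the accelerometer subset.

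Whether bias occurs depends on how the sequence was built in REDCap. Its direction cannot be predicted and its size is unknown. Under the assumed shifts and slopes it is about 0.4 to 5 points on a 10-point effect. The design has little margin for the attenuating case. Differential baseline non-response is a further possibility that cannot be sized from the article. The sample size is unaffected.

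It deserves correction because it concerns the primary estimate, is cheap to prevent and cannot be undone once the data are collected. The app-consent wording is a separate, smaller inconsistency and adds nothing to the weight of the main point.

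**What to change.** State one order in Participants and recruitment, Randomisation and blinding, and the accelerometer text: consent; baseline survey complete (plus the sensor week for the subset); randomisation; disclosure of allocation and app login. Set REDCap so that randomisation, or at least disclosure, opens only when the baseline form is marked complete. If this is already how the system works, a sentence saying so is enough.

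The article gives study dates from June 2024 and appeared in February 2025, so some participants may already be enrolled. For any who completed the survey after learning their group, use the survey and allocation timestamps to identify them. Add a sensitivity analysis of the primary model that does not rely on the post-allocation baseline, for example one unadjusted for it. Report baseline completion by arm.

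Separately, reconcile consent through the mobile application with the statements that only the intervention group has the app, for example by taking consent on paper or by e-consent outside it.

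Cost: a change of form logic and wording. Randomisation is delayed by minutes for most participants and by about a week or more for the sensor subset. People who consent but do not finish the baseline would not be randomised, so slightly more may need to be approached.
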